#### Main study parameter/endpoint

The primary endpoint will be pain experience 1 year postoperatively. This will be scored for RLP and PLP on an 11-point (0–10) Numeric Rating Scale (NRS) for 30 consecutive days and averaged. Patients will receive additional textual and visual information on how to differentiate between RLP and PLP in the questionnaires. We will use the Medication Quantification Scale to correct for pain medication use.^28^ Besides the NRS, pain will also be scored using the Patient-Reported Outcomes Measurement Information System (PROMIS) pain behaviour and interference short forms (7a and 8a, respectively) in Dutch.^29^

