## Introduction

### Background and rationale

 Approximately 2200 major lower extremity amputations, transfemoral to transtibial, are performed in the Netherlands each year, and the incidence is rising, particularly due to vascular disease.^1 2^ Around 61% of these patients develop postamputation pain (PAP).^3^ PAP is known to compromise prosthetic rehabilitation and profoundly diminish the quality of life after amputation.^4^ Patients with chronic pain report a lower health-related quality of life when a neuropathic component is present (0.70 vs 0.47).^5^ Moreover, it is associated with a significant burden on the healthcare system.^6^ Direct healthcare costs may comprise prehospital care, emergency care, hospitalisation, long-term postdischarge care and rehabilitation (eg, increased opioid use and other (neuropathic) pain medication and interventions by pain specialists to treat PAP). Indirect costs may arise as a consequence of loss of productivity for both patients and their families.

PAP falls into two major categories: residual limb pain (RLP, ‘stump pain’) and phantom limb pain (PLP). RLP has different aetiologies, including infection, vascular insufficiency, scar tissue, bone spurs and neuroma formation.^7^ PLP is caused by transection of the nerves during amputation. While the exact mechanism behind PLP is not yet fully understood, it is partly explained by deafferentation from the distal target. Currently, there is no uniform protocol for the surgical handling of nerves during amputations. There is little attention for nerve handling in surgical textbooks, the Dutch Guideline ‘Amputation and prosthetics of the lower extremity’ and the Global Vascular Guideline on the Management of Chronic Limb-Threatening Ischaemia do not mention nerve handling during amputation surgery.^4 8^ Today, techniques used depend primarily on traditions and expert opinions, which lack a solid scientific base. Nerve handling is performed with sharp transection or electrocautery, often using light traction or ligation. After the nerve is cut, it may be tucked away, coagulated, infiltrated with a local anaesthetic or alcohol or it may be left untreated.^9^

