### Outcomes

Longitudinal studies show no further improvement of PAP after TMR in amputees after 12 months postoperatively.^15 23 26 27^ Therefore, our follow-up time will be 12 months. Outcomes will be assessed at 2 weeks and at 3, 6, 9 and 12 months via questionnaires (table 1). These will be completed digitally via email, using a pseudo-anonymised data management platform. Patients allocated to the control group who experience significant pain at the end of the study will be offered additional TMR, regardless of amputation level.

**Table 1 T1:** Schedule of enrolment PreventPAP trial

Study period	Enrolment	Allocation	Postallocation						Close-out
Timepoint in Months	0	0	0.5	3	6	9	11	12	12
Enrolment:									
Screening/eligibility criteria	X								
Informed consent	X								
Allocation		X							
Assessment:									
Baseline characteristics	X	X							
Preoperative/intraoperative/postoperative variables	X	X							
Questionnaires:									
NRS RLP and PLP*				X	X	X		X†	
PROMIS Pain Behaviour 7a Short Form^29^				X	X	X		X†	
PROMIS Pain Interference 8a Short Form^29^				X	X	X		X†	
EQ-5D-5L^32^			X	X	X	X		X	
ICAN Pain Sketches^30^				X	X	X		X	
iMCQ and iPCQ^36 37^				X	X	X		X	
PainDetect^31^								X	
HADS^33^								X	
GPE-DV^34^								X	
PLUS-M^35^								X	
Close-out:									
Outcome									X
Medication‡									

* NRS for RLP and PLP will be measured every day for 30 consecutive days at 11 months postamputation.

† Primary endpoint.

‡ Medication will be recorded at the end of the study for the whole study period.

EQ-5D-5L, European Quality of Life - 5 Dimensions - 5 Levels; GPE-DV, Global Perceived Effect - Dutch Version; HADS, Hospital Anxiety and Depression Scale; ICAN, Interdisciplinary Care for Amputee Network; iMCQ, Medical Consumption Questionnaire; iPCQ, Productivity Cost Questionnaire; NRS, Numeric Rating Scale; PLP, phantom limb pain; PLUS-M, Prosthetic Limb Users Survey of Mobility; PROMIS, Patient-Reported Outcomes Measurement Information System; RLP, residual limb pain.

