#### Secondary study parameters/endpoints

Secondary endpoints include the use of analgesics or pain interventions, surgical time, length of hospital stay and adverse events or complications, including survival. In addition, multiple questionnaires will be sent to the participants regarding RLP and PLP during the study (measured by the NRS); pain behaviour and pain interference during the study (measured by the PROMIS Pain Behaviour and Pain Interference Short Forms)^29^; local, diffuse or radiating pain (measured by the Interdisciplinary Care for Amputee Network pain sketches)^30^; neuropathic pain (measured by the PainDetect)^31^; quality of life (measured by the European Quality of Life - 5 Dimensions - 5 Levels (EQ-5D-5L))^32^; anxiety and depression symptoms (measured by the Hospital Anxiety and Depression Scale)^33^; perceived treatment effect (measured by the Global Perceived Effect - Dutch Version)^34^ and mobility 1 year after surgery (measured by the Prosthetic Limb Users Survey of Mobility).^35^ A cost-effectiveness analysis (CEA; measured by the Medical Consumption Questionnaire (iMCQ))^36^ and the Productivity Cost Questionnaire (iPCQ)^37^ and a budget impact analysis (BIA) (measured by the ZonMw BIA tool) will also be performed at the end of the study. All data will be collected using validated questionnaires at different time points (table 1).

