### Sample size calculation

In studies of both chronic and acute pain, a change of two points on the NRS has been shown to be clinically relevant and correlated to a patient’s need to take additional pain medication.^38^ To detect a minimal clinically important difference of two points on the NRS, considering an SD of 3.5 from similar studies that measured pain at one time point after 12 months^15 23 26 27^ in a clinically heterogeneous group, with a significance level of 0.025, we need to analyse 2×76=152 patients to achieve 90% power. With an estimated loss to follow-up of 6%, we need to include 162 patients. Moreover, based on the study by Cascini *et al*^25^ and our clinical experience, we expect a 1-year mortality rate of 20% in our patient population aged 75 years or younger. With an estimated 1-year survival of this patient group of 80%, we need to include 203 patients in total. Due to the semiacute setting of most amputations, organising the availability of both extra operating time and a trained nerve surgeon might be a challenge. Therefore, we estimate including 40% of all major lower extremity amputations. To be able to randomise 203 subjects, we estimate the need to screen 508 patients (figure 2).

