#### Primary study parameter(s)

We selected four co-primary endpoints on the basis of the expected impact of the intervention and relevance for the patients. They are all primarily assessed at 12 months after surgery:

RLP (NRS).PLP (NRS).PROMIS Pain Behaviour Short Form (7 a).PROMIS Pain Interference Short Form (8 a).

These outcomes will be compared between the two treatment groups on the basis of the intention-to-treat principle. The comparisons will be adjusted for age, sex and amputation level, based on clinical relevance. To account for multiple comparisons, we proceed as follows. We start by testing outcomes 1 and 2 at a significance level of 0.025 (two-sided) using the Bonferroni correction. This is the basis of our sample size calculation. Next, we apply a serial gatekeeping procedure:

If both outcomes 1 and 2 reach statistical significance, outcome 3 will be tested at a significance level of 0.05 (two-sided). If outcome 3 reaches statistical significance at that level, outcome 4 will be tested at a significance level of 0.05 (two-sided).If either outcome 1 or 2 reaches statistical significance, outcome 3 will be tested at a significance level of 0.025 (two-sided). If outcome 3 reaches statistical significance at that level, outcome 4 will be tested at a significance level of 0.025 (two-sided).^39^

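### The article attaches a Medication Quantification Scale correction to the primary pain endpoint, but the primary analysis section has no such term; used as a covariate, it would no longer estimate the intention-to-treat effect.

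*Protocol article*

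**What the plan says.** Two sections of the protocol article describe the primary pain comparison differently.

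- *Main study parameter/endpoint* defines the endpoint as residual limb pain and phantom limb pain on the 0–10 numeric rating scale (NRS), scored on 30 consecutive days and averaged. It then adds: "We will use the Medication Quantification Scale to correct for pain medication use". The sentence does not say whether the MQS is a covariate, part of a composite or the basis of a sensitivity analysis.
- *Primary study parameter(s)* sets the analysis: "These outcomes will be compared between the two treatment groups on the basis of the intention-to-treat principle". The covariates follow: "The comparisons will be adjusted for age, sex and amputation level, based on clinical relevance". The MQS is not among them.

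Three other places show what kind of variable analgesic use is in this trial.

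- It is an outcome: "Secondary endpoints include the use of analgesics or pain interventions" (*Secondary study parameters/endpoints*).
- It is collected after randomisation: "Medication will be recorded at the end of the study for the whole study period" (footnote to Table 1).
- It follows from pain. *Background and rationale* lists among the costs of postamputation pain "increased opioid use and other (neuropathic) pain medication and interventions by pain specialists to treat PAP", and *Sample size calculation* describes the two-point NRS change as "correlated to a patient’s need to take additional pain medication".

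**The concern.** Read in its ordinary sense, a correction for medication means comparing pain between arms at equal analgesic use. That is safe for a baseline variable. Here the variable lies downstream of treatment. The trial's hypothesis is that TMR lowers pain, and the article says that pain drives medication. Holding medication fixed then removes part of the effect that the trial is meant to measure, and the arms being compared are no longer the randomised ones.

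The two NRS outcomes are tested first, each at 0.025, and their results decide whether and at what level the two PROMIS outcomes are tested. If the text allows both a medication-corrected and an uncorrected NRS analysis to be called primary, there are two possible primary results, and the choice between them carries down the whole testing sequence.

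**Working it through.** **1. The plan's own figure.** The inputs from *Sample size calculation* are a difference of 2, an SD of 3.5, alpha 0.025 (two-sided, from *Primary study parameter(s)*) and 90% power.

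n per arm = 2 × (2.2414 + 1.2816)² × 3.5² / 2² = 76.02, which the plan gives as 76, so 152 in total. Then 152 / 0.94 = 161.7, so 162, and 162 / 0.80 = 202.5, so 203. The figures reproduce, with power 0.900 at 76 per arm. They contain no allowance for an MQS correction.

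**2. What a covariate would do.** In a linear model with treatment and MQS:

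adjusted effect = total effect − (within-arm slope of NRS on MQS) × (treatment difference in MQS)

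With r the within-arm NRS–MQS correlation and d the TMR effect on MQS in SD units, this is −2 − 3.5 × r × d.

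**3. Case A: MQS tracks pain (assumed).** Let MQS equal pain plus noise with SD s. Then r = 3.5 / √(3.5² + s²) and d = −2r / 3.5, so the adjusted effect is −2(1 − r²). The standard error is 3.5 × √(1 − r²) × √[(2/76)(1 + d²/4)], and power is Φ(|effect| / SE − 2.2414).

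| s | r | adjusted effect | SE | power |
|---|---|---|---|---|
| 9 | 0.36 | −1.74 | 0.532 | 0.85 (0.84 by simulation) |
| 6 | 0.50 | −1.49 | 0.495 | 0.78 |
| 3.5 | 0.71 | −1.00 | 0.410 | 0.58 |

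**4. Case B: r and d set separately (assumed).**

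- r = 0.2, d = −0.25: −2 + 0.175 = −1.82, power about 0.85.
- r = 0.5, d = −0.5: −2 + 0.875 = −1.12, power about 0.49.
- r = 0: −2.00, no bias.
- r = −0.2, d = −0.25 to −0.5: −2.17 to −2.35, so the effect is overstated.

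**5. Case C: medication also relieves pain (assumed).** Take Case A with s = 6, and let each MQS unit lower the reported NRS by 0.3. The unadjusted effect is −2 × (1 − 0.3) = −1.40. The within-arm slope is 12.25 / 48.25 − 0.3 = −0.046, so the adjusted effect is −1.40 − (−0.046)(−2) = −1.49. The shift is small and goes the other way. A second mechanistic scenario, in which MQS rises 0.5 per pain point and relieves 0.2 NRS points per unit, gave −1.80 unadjusted and −1.00 adjusted.

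The documents give neither r nor d, so steps 3 to 5 show a range of consequences and do not estimate what will happen.

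**The case against.** The strongest reply is that the article never says the MQS is a regression covariate. The section that specifies the primary model leaves it out, and *Statistical analysis* names the same three covariates. If that section governs, there is no MQS term, no bias arises and the 90% power stands. The form of the correction is also a detail that a condensed article may leave to the full protocol or analysis plan. And the aim is legitimate: equal pain scores do not mean the same thing if one arm needs more analgesics to reach them.

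Much of this stands. A reader might infer that the primary effect is biased as a settled fact, or that the stated power is wrong. The documents support neither, because both depend on the covariate reading and on correlations that are not given. A reader might also infer that the medication data are error-prone because they are recorded once, at study end. The Table 1 footnote does not state the source, and extraction from records is not excluded.

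What does not fall away is the conflict. The correction is stated without qualification, directly after the definition of the primary endpoint, and is not labelled supportive. Read as a covariate or as a composite, it does not match the primary analysis section; a supportive analysis would be compatible, but the article does not say that this is meant. The missing detail may belong elsewhere, but the disagreement is in this document.

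**Conclusion.** The point holds as a conflict over the primary estimand, with a conditional consequence. The endpoint section promises a medication correction by a variable that is post-randomisation, is a listed outcome and, on the article's own account, responds to pain. The analysis section defines an intention-to-treat comparison without it.

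If the MQS were used as a covariate and tracked pain with a within-arm correlation of about 0.36 to 0.7, a 2.0-point effect would appear as about 1.7 to 1.0 points, with power of about 84% to 58% instead of 90%. Attenuation is the more plausible direction given how the article links pain and medication. Zero bias or overstatement is possible under other assumptions. If the MQS were instead combined with the NRS, the result would be a different estimand, to which the 2-point difference and the SD of 3.5 do not apply.

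**What to change.** 1. Remove the MQS correction from the primary NRS analysis. State in the endpoint section that the primary comparison is the intention-to-treat difference in NRS regardless of analgesic use, adjusted only for age, sex and amputation level.
2. Report the MQS as a secondary outcome, in line with the existing analgesic-use endpoint.
3. If a medication-integrated result is wanted, label it supportive and pre-specify its form (for example a joint NRS–MQS rank) and its time window. The NRS covers 30 days from month 11, while medication is recorded for the whole study period, so the window that feeds the MQS must be named.
4. Settle this before any unblinded outcome data are seen.

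The cost is a few sentences in the protocol and analysis plan, with no extra patients and no change to the sample size. Adding medication items to the 3, 6, 9 and 12-month questionnaires would help place use in time, but it is optional.

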#### Secondary study parameters/endpoints

Secondary endpoints include the use of analgesics or pain interventions, surgical time, length of hospital stay and adverse events or complications, including survival. In addition, multiple questionnaires will be sent to the participants regarding RLP and PLP during the study (measured by the NRS); pain behaviour and pain interference during the study (measured by the PROMIS Pain Behaviour and Pain Interference Short Forms)^29^; local, diffuse or radiating pain (measured by the Interdisciplinary Care for Amputee Network pain sketches)^30^; neuropathic pain (measured by the PainDetect)^31^; quality of life (measured by the European Quality of Life - 5 Dimensions - 5 Levels (EQ-5D-5L))^32^; anxiety and depression symptoms (measured by the Hospital Anxiety and Depression Scale)^33^; perceived treatment effect (measured by the Global Perceived Effect - Dutch Version)^34^ and mobility 1 year after surgery (measured by the Prosthetic Limb Users Survey of Mobility).^35^ A cost-effectiveness analysis (CEA; measured by the Medical Consumption Questionnaire (iMCQ))^36^ and the Productivity Cost Questionnaire (iPCQ)^37^ and a budget impact analysis (BIA) (measured by the ZonMw BIA tool) will also be performed at the end of the study. All data will be collected using validated questionnaires at different time points (table 1).

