### Objective and hypothesis

In this study, we aim to compare primary TMR with traction neurectomy during a transfemoral to transtibial amputation as a primary or secondary sequela of vascular disease. We hypothesise that primary TMR will decrease PAP and improve quality of life at lower costs.

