### Study population

The study population includes patients who receive a major amputation of the lower extremities as a primary or secondary sequela of vascular disease. To ensure a homogenous cohort, only patients with an amputation as a result of vascular pathology are included. In the Netherlands, this group accounts for 90%–95% of all amputations of the lower extremities.^4^ Moreover, as age above 75 years is a major risk factor for 1-year mortality, this group was excluded.^25^

Inclusion criteria

Patients aged between 18 and 75 years.Scheduled for a transtibial, through-knee or transfemoral amputation as a primary or secondary sequela of vascular disease.

Exclusion criteria

Insensate limbs at the level of amputation.Complex Regional Pain Syndrome.Existing neuroma or prior neuroma surgery in the affected limb.Undergoing radiotherapy on the affected limb.Cognitive impairment or delirium at the time of consent.Patients who are unfit for general anaesthesia.No nerve surgeon trained in the TMR procedure is available.

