#### Secondary study parameters

All secondary study parameters will be compared using the appropriate tests, which are subsequently adjusted for age, sex and amputation level. Categorical variables will be analysed using the χ^2^ test or Fisher’s exact test and adjusted with a logistic regression model. Continuous variables will be assessed using the Student’s t-test or Mann-Whitney U test and adjusted using a linear regression model.

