Depending on the literature source and the level of amputation, the frequency of PAP ranges between 33% and 86%.^3^ In the patient series performed on primary TMR, PAP was present in 8%–29%.^1719^,^22^ After primary TMR, 90.9% of patients who had TMR were ambulatory compared with 70.5% (p<0.01) in the amputation-only group. O’Brien *et al* showed a longitudinal durability of this effect over 18 months or more in 81 patients.^23^ One trial on TMR as a secondary procedure^14^ showed an average decrease in pain NRS of 3.2 in the TMR arm compared with an average increase of 0.2 in the standard treatment arm. Various cohort studies on secondary TMR show similar results.

Primary TMR results in a reduction of the chance of developing PAP. The risks and the burden for patients are negligible.

Because the risks of TMR are negligible, no data safety management board has been assigned. During the study, patient safety and execution of study procedures will be closely monitored by an independent clinical trial monitor and auditor according to local regulations.

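### The only named mobility measure is a survey for prosthesis users, so a comparison of scored patients would be in a post-randomisation subgroup and may understate a TMR benefit

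*Protocol article*

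**What the plan says.** Under Secondary study parameters/endpoints, the protocol article lists "mobility 1 year after surgery (measured by the Prosthetic Limb Users Survey of Mobility". Table 1, under Outcomes, schedules it once, at 12 months, and its footnote spells the instrument out as "PLUS-M, Prosthetic Limb Users Survey of Mobility". No other mobility instrument is named. Neither prosthesis use nor ambulatory status appears among the listed endpoints.

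The inclusion criterion on surgery reads "Scheduled for a transtibial, through-knee or transfemoral amputation as a primary or secondary sequela of vascular disease". Being a candidate for a prosthesis, or being fitted with one, is not a criterion.

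Three statements link treatment to prosthesis use or walking:
- Background and rationale: "PAP is known to compromise prosthetic rehabilitation and profoundly diminish the quality of life after amputation".
- Objective and hypothesis: "We hypothesise that primary TMR will decrease PAP and improve quality of life at lower costs".
- Benefits and risk assessment: "After primary TMR, 90.9% of patients who had TMR were ambulatory compared with 70.5% (p<0.01) in the amputation-only group".

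For analysis, Secondary study parameters gives only the general rule "Continuous variables will be assessed using the Student’s t-test or Mann-Whitney U test and adjusted using a linear regression model", with age, sex and amputation level as covariates. Categorical outcomes get a logistic model.

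**The concern.** A patient who never receives a prosthesis, or has stopped using one, is outside the group that the survey is named for. Prosthesis use at 12 months arises after randomisation. On the article's own reasoning, TMR lowers pain, pain hampers prosthetic rehabilitation, and more patients walk after TMR. The share of patients who can be scored may therefore differ by arm.

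If TMR brings additional, less mobile patients into prosthesis use, they enter the TMR mean at the low end, while similar control patients contribute no score. Adjustment for age, sex and amputation level does not undo that selection. The repeated-measures analysis cannot help either, because PLUS-M has no earlier measurement to borrow from. At stake is the interpretation of the one mobility result: a real benefit could look smaller than it is. The ambulation difference that the article cites as a benefit could also not be tested by randomised comparison if walking status is not collected.

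**Working it through.** **The plan's own figures.** No figure is stated for mobility. The sample size for the pain scores supplies the number analysed per arm, and it reproduces: 2 × (2.241 + 1.282)² × 3.5² / 2² = 76.0 per arm. Then 152 / 0.94 = 161.7, so 162, and 162 / 0.80 = 202.5, so 203.

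**Inputs.**
- Shares able to give a score: 70.5% control and 90.9% TMR, from Benefits and risk assessment. These are ambulatory shares, used here as a proxy.
- Correlation ρ between the tendency to use a prosthesis and mobility: not in the document, so varied from 0 to 1.
- Mobility expressed in SD units and assumed normal.

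**Patients with a score.** Control: 76 × 0.705 = 53.6. TMR: 76 × 0.909 = 69.1. About 54 and 69 patients are scored. Without a score are 29.5% of control and 9.1% of TMR patients, or (152 − 122.7) / 152 = 19% overall.

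**Formula.** In each arm, the scored patients are the top share p on the tendency to use a prosthesis. Their mean mobility exceeds the whole-arm mean by ρ × φ(c) / p, where c is the standard normal quantile at 1 − p and φ is the normal density.
- Control: c = −0.539, φ(c) / p = 0.489.
- TMR: c = −1.335, φ(c) / p = 0.180.

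With a true mean difference δ, the difference among scored patients is δ + ρ × (0.180 − 0.489) = δ − 0.309ρ.

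| ρ | Bias (SD) | True 0.2 SD appears as | True 0.5 SD appears as |
|---|---|---|---|
| 0 | 0 | 0.20 | 0.50 |
| 0.3 | −0.09 | 0.11 | 0.41 |
| 0.5 | −0.16 | 0.05 | 0.35 |
| 0.7 | −0.22 | −0.02 | 0.28 |
| 1.0 | −0.31 | −0.11 | 0.19 |

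A true benefit of 0.2 SD changes sign only when ρ exceeds 0.2 / 0.309 = 0.65. A true benefit of 0.5 SD shrinks but is never reversed.

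**Other assumed shares.** For 50% against 65%, the bias is −0.07 to −0.23 SD for ρ from 0.3 to 1.0. For 40% against 50%, it is −0.05 to −0.17 SD.

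**The case against.** The strongest reply is that the article nowhere restricts the PLUS-M analysis to users. It says that questionnaires go to the participants, and Table 1 adds no restriction. How non-users are scored is a rule that commonly sits in the full protocol or SAP, neither of which is shown. The Mann-Whitney option would even accommodate ranking non-users lowest in the unadjusted test. What the instrument does with non-users is set out in a cited source that is not available here. This stands: a users-only comparison is inferred from the instrument's name and the general analysis rule, and is not written down.

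It is also fair that the cited 90.9% and 70.5% are ambulatory shares from earlier work. They are neither shares of prosthesis users nor assumptions of this trial. Mobility is an unpowered secondary outcome outside the gatekeeping sequence, and it is not among the aims under Objective and hypothesis. The endpoint list is introduced as non-exhaustive, so prosthesis status might already be on a case report form.

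What the reply does not remove is the choice of instrument, which this document fixes. A later analysis plan can set a scoring rule for non-users, but it cannot recover walking or prosthesis data that were never collected.

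**Conclusion.** The point holds as a cheap improvement to a secondary outcome. The sole named mobility measure is aimed at prosthesis users, the population is not selected for prosthesis use, and the plan's reasoning makes such use something that TMR may change. If scored patients alone are compared, the bias against TMR is about 0.09 SD at ρ = 0.3, 0.16 SD at 0.5 and at most 0.31 SD at 1.0, with none at 0. This rests on the ambulatory shares as a proxy for scoreability, normality, and an actual difference in use between arms.

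A reader might go further and infer that the comparison will hide or reverse a benefit, or that the trial cannot say anything about mobility. The documents do not support that. The largest figures (a true difference of 0.80 SD reported as 0.80 − 0.31 = 0.49 SD, about 40% too small, or an apparent disadvantage of 0.31 SD with no true difference) require use to be fully determined by mobility. Attenuation is the general result; reversal needs a small true benefit or a strong correlation. The primary analysis and the sample size are untouched.

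**What to change.** Record prosthesis use and ambulatory status (each yes/no) at 12 months in every surviving randomised patient, list them as secondary outcomes, and compare them by randomised group with the logistic model already given for categorical outcomes. If the case report form already holds these items, only the listing and the comparison need adding.

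State that the PLUS-M mean among users is descriptive. Optionally, add a rank analysis of all survivors that places non-users lowest. The Mann-Whitney test already serves for the unadjusted version; the adjusted version would need an ordinal model in place of linear regression.

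The cost is one or two questionnaire items, a change to one secondary analysis and, for the rank analysis, a result that is harder to express in PLUS-M points. The items need to be in place before 12-month follow-up is completed. The parallel registry is to send the same 12-month questionnaires apart from those on cost-effectiveness, so adding the items there too would keep the two cohorts comparable.
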